# A protocol for a pilot cluster randomized control trial of e-vouchers and mobile phone application to enhance access to maternal health services in Cameroon

**DOI:** 10.1186/s40814-020-00589-y

**Published:** 2020-04-14

**Keywords:** mHealth, Vouchers, Maternal mortality, Family planning, Reproductive health, Cluster randomized control trials, Qualitative research, Geographic information system, Pilot, Feasibility

## Abstract

**Background:**

Cameroon still has relatively high maternal mortality rate (MMR) of 596/100,000 live births. Approximately 40% of births are unattended by skilled healthcare personnel with high out-of-pocket expenditures. Poor resource allocation, poorly functioning referral systems, long trekking distances to health facilities, all of which lead to low rates of use of maternal health services.

**Objectives:**

The aim of this pilot study is to explore perception and acceptability of mobile health (mhealth) and e-voucher and to determine the feasibility of conducting a large cluster randomized trial to determine the effects of combining e-vouchers and a mobile application compared with usual care in improving access to and use of maternal health services.

**Methods:**

This is a multimethod study that comprises two phases. The first phase is the development of the mobile phone app, which includes a qualitative formative study through in-depth key informant interviews and focus group discussions. The second phase is a cluster randomized control trial assessing the combination of e-vouchers and a mobile application compared with usual care in improving access to and use of maternal health services. Feasibility will be determined based on evaluating randomization, contamination, enrollment rate, complete follow up, compliance rate, success in matching data from different sources, and data completeness.

**Ethics and discussion:**

Ethics approval has been granted, and the trial has been registered in the Pan-African Clinical Trials Registry. We will disseminate our findings through peer-reviewed manuscripts and conference presentations. Findings from this study will inform the design and conduct of a larger randomized trial.

**Trial registration:**

PACTR201808703097367. The trial on the Pan African Clinical Trials Registry.

## Background

Despite tremendous efforts to improve maternal and child health in developing countries, there are indications that low-income individuals have not benefited much in the areas of maternal and child health [1]. In Africa, most women are unable to seek health care due to high out-of-pocket costs [1–12]. Systematic reviews on voucher interventions in addressing maternal mortality have shown that vouchers can be effective in improving access to and utilization of maternal health services, especially in poor and underserved communities [11–26]. Vouchers typically grant purchasing power to low-income individuals who may otherwise be ignored in the market due to their lack of funds or knowledge of goods and services [18, 19].

Cameroon is a lower-middle income country with a relatively high maternal mortality rate (MMR) of 596/100,000 live births [2–5]. Approximately 40% of births are unattended by skilled healthcare personnel [2–9], with approximately 35% of deliveries occurring at home [8]. Approximately 85% of women in Cameroon, especially rural women, have never received family planning education from a healthcare professional [8]. Women of reproductive age continue to die from pregnancy-related causes in Cameroon [2–5]. One potential factor associated with this stagnant progress toward achieving a considerable decline in maternal mortality is the low percentage (64%) of women delivering in hospitals [2–9]. This finding has been attributed partly to the policies that affect the healthcare delivery system, especially with respect to resource allocation and poorly functioning referral systems, coupled with the introduction of user fees in the public health sector [2–9], resulting in an out-of-pocket per capita expenditure of 94.6% [2].

In 2011, a performance-based financing (PBF) pre-pilot program was initiated in Cameroon, covering four health districts, with a focus on maternal and child health and communicable diseases, especially in certain vulnerable groups such as the poor, women, children, and people living with human immunodeficiency virus (HIV)/acquired immunodeficiency syndrome (AIDS) [2]. In July 2012, the program was expanded to the northwestern and southwestern regions of Cameroon. PBF is a strategy in which providers are paid based on their output with respect to a predefined quality standard to improve the quality of care delivery, especially for maternal health services [2]. Cameroon has adopted PBF as a national strategy toward achieving universal health coverage.

Digital health is currently revolutionizing the delivery of health services, most importantly reproductive, maternal, newborn, and child health (RMNCH) services, in developing countries [27, 28]. Systematic reviews have shown mobile phones to be effective in delivering maternal health education, advice, and support [27, 28]. However, reported challenges have been noted in the utilization among nonliterate groups, especially in rural areas. In addition, there are challenges in accessing RMNCH services during emergencies, especially in hard-to-reach communities with difficult terrains, little or no constant power supply, and poor networks. In some areas, there are practically no motorable roads; thus, women trek considerable distances before reaching a health center or reaching any means of transportation.

Our aim is to incorporate vouchers (a demand-side strategy) and mobile phone applications into the healthcare delivery system to complement the newly implemented PBF in Cameroon, which has the potential to boost the quality of provider performance as a supply-side mechanism to enhance sustainability. This study seeks to address whether implementation of vouchers, concurrently with PBF, will help reduce the barriers associated with delays in accessing maternal health care services. This will also inform subsequent research aimed at scaling-up e-vouchers and mobile phone interventions to improve maternal health.

### Objectives

The aim of this study is to explore perception and acceptability of using mhealth and e-voucher in delivery RMNCH and to determine the feasibility of conducting a cluster randomized trial to increase access and utilization of antenatal care, skilled birth delivery, and family planning awareness among rural poor women in Cameroon using targeted e-vouchers and mobile phone applications. This study integrates e-vouchers within the PBF platform concurrently to deliver maternal care services. The study will assess the feasibility of the processes involved, management of resources, mobile phone application software, and resources used.

## Methodology

### Theoretical framework

Three conceptual frameworks are considered in this study: The first framework is the three delays model by Thaddeus and Maine (1998), which maps out key factors (delays) at various stages that may affect the intervention [29]. This model was considered in the design of the platform for the mobile phone applications and to explore the experiences of the community to map out contextual barriers to accessing reproductive maternal and child health services and to inform or modify aspects of interventions and features of the mobile application where applicable. The second framework is the Anderson behavioral theory on healthcare utilization; this will assess health-seeking behavior and utilization of RMNCH [30], which is a function of three characteristics [30].The third framework is the transtheoretical model [31, 32], which we will use to understand and map out the five stages of health behavior change within the community in relation to family planning. This framework and these stages will be used to develop social marketing messages for the family planning intervention, which will be based on the community’s needs [31–34].

The rationale for using the three frameworks above is based on the hypothesis that access to services does not necessarily translate to utilization of services. Thus, the three delays model is used to map out the contextual barriers in accessing RMNCH services at different stages, and to guide the development of the mobile application and help inform specific or relevant areas of intervention and modification of the mobile app. The transtheoretical model is specific to understanding the behavioral change process and stages of the family planning aspect to help develop the messages that will be incorporated within the family planning icon, while the Anderson behavioral model will be used to understand the process of the intervention and utilization of services at different levels (see Fig. 1).

**Fig. 1 Fig1:**
[figure not shown]
Project framework

### Study design

The study is a multimethod study that follows an exploratory sequential design [35–37]. The study is comprised of two phases: a formative study through key informant interviews and focus group discussions, followed by a cluster randomized control trial including a follow-up focus group discussion for post-intervention groups. The rationale for using this exploratory design is that the formative phase will inform some aspects of the intervention from the outset and the mobile application. This is also an important criterion, as recommended in the guidelines for mhealth evidence reporting and assessment [38]. In addition, the data from the formative study will provide supportive information and findings that can be easily generalized within the context.

### Setting, context, and population

The intervention will be carried out in the Bali and Ndop Health Districts. These health districts are in the northwest region of Cameroon and are rural areas. The population sizes of these health districts are as follows: Bali: 73,614, Ndop: 218,505.

### Study districts

The study districts will be purposefully selected because the district medical officers approved of the implementation of the intervention trial in their respective districts. We planned to stratify PBF and non PBF districts into intervention and control districts; however, with the adoption of PBF as a national strategy, the project may take a pragmatic approach if the non-PBF district eventually gets enrolled into PBF.

#### Phase I: formative study for intervention development

##### Objective

The objective of this phase is to explore the community’s experiences in accessing RMNCH and their perception and acceptability of using mhealth in the delivery of RMNCH care. This phase will explore the perspectives of pregnant women, relevant stakeholders, and health care providers.

##### Sampling

i.Sample size and enrolment

Purposive sampling will be used to initially recruit participants for the key informant interviews and focus group discussions. The snowballing technique will be used to reach out to pregnant women who do not have access to the health center. Sampling in each group will continue until emergent themes begin to appear [39–41].

The study aims to explore the following outcomes—community perception and acceptability of using mobile phones and e-vouchers in the delivery of maternal health services and their experiences. The outcome will help to refine features of the app and to understand and inform how changes in behavior are initiated and how they can be sustained.
ii.Enrolment

Women who have given birth, pregnant women, and/or breastfeeding mothers will be eligible for the KI interviews, in addition to key informants as identified within the community during stakeholder meetings. A minimum of six and maximum of eight participants (both men and women) will be enrolled in each focus group discussion. Participants for focus group will be recruited using a theoretical sampling approach.
iii.Data generation

The formative study will explore the following sociocultural and structural factors associated with the access to and utilization of maternal health services: the barriers and facilitators during pregnancy; the participants’ perception of antenatal care, skilled birth delivery, and family planning; their experiences with using maternal health services; and their perception of using mobile phones in delivery care. Components as well as the sociocultural and structural factors that facilitate or hinder the providers’ quality of delivery care will also be assessed. Focus group discussions including 6–8 members will be conducted separately for both men and women. The post-intervention focus group will explore their experiences in using the mobile phones and their difficulties, and feedback and recommendations will be solicited to improve and refine the mobile application.
iv.Qualitative data analysis approach

The data analysis will include a directed content analysis, which starts with a theory (for example, the three delays model) or relevant research findings as guidance for the initial codes [39–41]. Transcribed text that describes any of the three delays will be highlighted, and a deductive approach will be used in all highlighted text, which will be compared and sorted using all predetermined categories of all the delays. Specifically, for family planning, we will upload transcripts to MaxQDA (https://www.maxqda.com/) and develop codes using grounded theory approach. Next, we will visualize all the data on MaxQDA using maps, emerging themes and modeling, and we will retrieve and export results as code books, maps, or themes.

We will use results from the formative study to develop a social marketing strategy for behavior change using the transtheoretical model [31–34] to map out the stages of change for the uptake of family planning and antenatal care services. Finally, we will identify the five levels of change using barriers and enablers identified from key informants and focus group discussion narratives and use these findings to design binary pictorial decision aids for the uptake of family planning and antenatal care services.

#### Development of the application and theory of change for the intervention

The development phase of the application involved continuous consultations with relevant stakeholders, including health providers, district medical officers, and community members within the specific context and literature reviews. These processes involved key informant interviews and focus group discussions to inform the intervention and refine the features, as well as to ensure project buy-in and to identify relevant contextual barriers and conditions to facilitate the intervention and ensure availability of the necessary resources to implement the intervention to achieve the desirable outcomes. The theory of change is attached as supplemental material (suppl figure 1) with examples of assumptions, the rationale, and some aspects of the intervention highlighting the various pathways of the intervention (suppl table 1). The final theory of change (ToC) will be updated at the end of the project after consultation with relevant stakeholders and user feedback evaluation including lessons learnt during the implementation processes.

#### Phase II: protocol for cluster randomized trial of electronic vouchers and a mobile application

##### Objective

To determine the feasibility of conducting a cluster randomized trial to increase access and utilization of antenatal care, skilled birth delivery, and family planning awareness by assessing the processes involved, management of resources, the mobile phone application software, and resources used.
i.Stratification and randomization

We will stratify health areas according to their equity scores (a higher equity score defines how remote or rural the area is, the distance from the district health service, and the enclaved nature of the topography with poor accessibility). Therefore, health areas with equity scores of ≥ 40 in the two participating health districts (Bali and Ndop) will be included. The second stage of stratification involves health areas with equity scores of ≥ 40 with a medicalized health center. All health areas with equity scores of ≥ 40 with no medicalized health center will be excluded at this stage. A medicalized health center implies the presence of a physician. Three health areas in Ndop meet the inclusion criteria with a ≥ 40 equity score and a medicalized center, namely Bambalang, Babesi, and Balikumbat. However, considering that the study requires two health areas, one for intervention and one for control, Balikumbat (equity score 42) will be excluded because it has a lower equity score than Bambalang (equity score 47) and Babesi (equity score 47). Bambalang and Babesi will be further randomized into a control and intervention health area via computer number generation. In the Bali district, Bosa and Nakka had the highest equity scores and had a medicalized center.

After stratification, a health facility assessment will be conducted to ensure the quality of health facilities for the intervention using the WHO Service Availability and Readiness Assessment (SARA) tool [42]. Health facilities will be assessed using this tool based on the context of Cameroon to ensure the quality of the services to be delivered and to ensure that all facilities are of equal standard and have the minimum required services to deliver the intervention, followed by the randomization of health areas into intervention and control groups using computer number generation (Fig. 2).

**Fig. 2 Fig2:**
[figure not shown]
Graphical presentation of CRCT

## Participants

The study is open to women aged 15–49 (with the current report of underage pregnancy ages of < 15, we anticipate adjusting the age to 13–49 years because this age group is not only vulnerable but also at high risk). Participants must also be ≤ 4 months pregnant and fall within the poverty scale of the study. Any comorbidity that is present at the time of the study that has a direct and/or indirect effect on antenatal care or the life of the woman or her unborn child will be treated appropriately as emergencies within the study (in the intervention group). This step will be performed after the randomization of the health areas into intervention and control groups. Participants in both groups will regularly interact with community health workers.

## Eligibility criteria

Inclusion criteria
Women aged 13–49 years, ≤ 4 months pregnantResident in the study area during the entire pregnancyProvision of informed consent for study participationMeeting the income bracket as defined by the tool that will be employed in the study

Exclusion criteria
Above the income bracket as defined in the studyPregnancy beyond 4 monthsRefusal to provide informed consent

The rationale for excluding women who are more than 4 months pregnant is to allow time to study the outcome of the intervention. The rationale for setting the minimum age of 13 years is due to the current outbreak of teenage pregnancy in these districts (www.ebaseafrica.org) because of the current educational crisis resulting from political instability. The ethics board approved of this age with an accompanying assent form.

## Sample size

The estimated sample size for the anticipated larger study was calculated using clinical outcome variables and using two-sided Z test statistics [43]. The final sample size calculation was computed using WINPEPI by Abramson (2004) [44]. The sample size calculation assumed and estimated that 20% of the individuals in the poorest quintile do not receive more than two antenatal care visits and are less likely to deliver by a skilled birth attendant in Cameroon [2–8]. Previous studies reported an approximately 10–15% increase in the use of antenatal care and a 10% increase in the use of skilled delivery [18–26]. Thus, the study assumes a 15% difference compared with the control assuming an inter-cluster coefficient of 0.001 [26, 45, 46], with four clusters. The study will need a sample size of 160 in each arm and a total of 320 individuals to obtain a 5% significance level and 80% power, assuming a loss to follow up of approximately 5%. The sample size when inflated yields 168 in each arm, a total of 84 in each group and a total of 42 in each cluster. Considering that this is a pilot feasibility study, the final sample size was determined by applying the criteria described by Wittes and Brittain (1990) [47] and Teere et al. (2014) [48] (if the sample size assumes a minimum compliance rate of 70% for the pilot RCT, a 50% sample size for the main trial is recommended, and Teere et al. (2014) also recommended a size of 60/group for a pilot study). Based on these recommendations for the pilot study, we defined a final sample size of 140 participants per arm, 70 in each group, and a total of 35 in each cluster. This sample size is large enough to meet the expectations of a pilot C-RCT and to account for potential loss to follow up.

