#### Secondary outcomes

The secondary outcomes include operational and economic outcomes, which assess the resource utilization involved, and management of the software as follows: human resource capacity, equipment availability, district and health area capacities, project timeline, and cost. These outcomes are operationalized in Table 1.

**Table 1 Tab1:** Table indicating feasibility, clinical, operational, and economic outcome variables

Outcome measures	Scale	Type	Measure	Method of analysis
Feasibility outcomes				
Evaluate randomization	Ordinal	Binary	% of health areas with successful stratification and randomization	Feasibility threshold of 95%
Enrolment rate	Nominal	Binary	% of participants with successful enrolment within 6 months into the trial	Feasibility threshold of 50%
Complete follow-up	Ratio	Continuous	% of participants who complete follow-up at 8months into the trial	Feasibility threshold of 80%
Compliance rate	Ratio	Continuous	% of participants who do not follow procedure as allocated	Feasibility threshold of 10%
Contamination	Ratio	Continuous	% of contamination	Feasibility threshold of 10%
Refusal rate	Ratio	Continuous	% of participants who refused to respond	Feasibility threshold of 5%
Adherence rate	Ratio	Continuous	% of participants who adheres to the intervention	Feasibility threshold of 80%
Clinical outcomes				
Failure rate	Ratio	Continuous	% of participants whom intervention (mobile phone features) failed to function according to design	*n* (%)
Mortality	Ratio	Binary	Number of maternal deaths	*n* (%)
Number of ANC visits	Nominal	Binary	Number of ANC visits attended	Mean (SD)
Number of skilled birth delivery	Nominal	Binary	Number of skilled birth delivery	Mean (SD)
Family planning	Nominal	Binary	% using family planning/awareness	*n* (%)
Operational outcomes				
Resource capacity	Nominal	Binary	Average number of human resources	Mean (SD)
Equipment availability	Nominal	Binary	Average number of equipment	*n* (%)
District and health areas capacity	Nominal	Binary	% of resource functionality and communication network	*n* (%)
Project timelines	Nominal	Binary	Average length of follow-up	Mean (SD)
Data collection time	Nominal	continuous	Average time to collect data	Mean (SD)
Matching data from other sources	Nominal	binary	% of success in matching data sources	*n* (%)
Data completeness	Nominal	Binary	% of participants who do not provide complete response	*n* (%)

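### The 80% power stated for the larger study ignores the 2 degrees of freedom left by two health areas per arm (about 38% on inputs that reproduce 160 per arm), and the base rate, direction and cluster breakdown do not match the calculation as worded.

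*Protocol article*

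**What the plan says.** The Sample size section says that its calculation is for a later trial: "The estimated sample size for the anticipated larger study was calculated using clinical outcome variables and using two-sided Z test statistics". The base rate is that "20% of the individuals in the poorest quintile do not receive more than two antenatal care visits". The effect and clustering inputs are that "the study assumes a 15% difference compared with the control assuming an inter-cluster coefficient of 0.001", with four clusters. The result is "The study will need a sample size of 160 in each arm and a total of 320 individuals to obtain a 5% significance level"; the power claimed is 80%. Allowing for 5% loss, this becomes 168 per arm, broken down as 84 per group and 42 per cluster. The pilot is then set at 140 per arm by reference to published pilot-study rules, broken down as 70 per group and 35 per cluster.

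On the number of clusters, Phase II (Stratification and randomization) takes one intervention and one control health area in Ndop and names two areas in Bali. Recruitment and follow up gives eight community health workers, two per health area. Both point to four health areas in total.

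In Table 1, the antenatal care (ANC) row ("Number of ANC visits attended") and the skilled birth delivery row are both typed as binary, yet both are to be summarised as mean (SD).

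**The concern.** A Z test treats the between-cluster variance as known. With two randomised areas per arm, it has to be estimated from very few units, and the reference distribution is far wider than the normal. A power figure that ignores this is too high however many women each area contributes.

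The inputs also do not read as the calculation appears to have used them. The 20% describes women who miss the visit target, the cited evidence concerns increased use, and the 15% has no stated direction. The arm, group and cluster labels do not add up for four areas.

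At stake is the planning of the larger trial, which this pilot exists to inform. A reader taking the paragraph at face value would carry forward a sample size, an ICC and a cluster count that do not together give the stated power.

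**Working it through.** **Inputs from the Sample size section:** two-sided 5% level, 80% power, base rate 20%, difference 15% (read as absolute), ICC 0.001, four clusters, 160 per arm, 5% loss. **From Phase II and Recruitment and follow up:** 8 workers / 2 per area = 4 areas, two per arm. **My assumptions:** ICCs of 0.01 and 0.05, used only to show a range.

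**1. Reproducing 160.** For proportions p1 and p2 with mean p and difference d:

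n0 = [1.96·√(2p(1−p)) + 0.8416·√(p1q1 + p2q2)]² / d²

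- 20% vs 35%: p = 0.275, so n0 = [1.96·√0.39875 + 0.8416·√0.3875]² / 0.0225 = 137.9.
- Continuity correction, n0/4·[1 + √(1 + 4/(n0·d))]²: 151.0.
- Design effect 1 + (m − 1)·0.001: for m = 40, 151.0 × 1.039 = 157; for m = 80, 151.0 × 1.079 = 163. The stated 160 lies in this range.
- Without the correction: 137.9 × 1.039 = 143 to 137.9 × 1.079 = 149, which is too low.
- Loss: 160 × 1.05 = 168, as stated.

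The pair 80% vs 65% gives the same n. The other direction, 20% falling to 5% (equivalently 80% rising to 95%), gives n0 = 75.1, or 87.9 corrected. With two clusters per arm and ICC 0.001 these become about 78 and 92 per arm. So with the stated 20% and 15%, 160 is reached only as 20% vs 35% with continuity correction.

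**2. Power with the degrees of freedom counted.** SE = √[DE·(p1q1 + p2q2)/n], with n = 160 per arm and DE = 1 + (m − 1)·ICC. For two clusters per arm, m = 80. At ICC 0.001, DE = 1.079, SE = √(1.079 × 0.3875/160) = 0.0511, and the noncentrality is 0.15/0.0511 = 2.93. The last two columns use the noncentral t distribution (critical values 4.30 on 2 df and 2.45 on 6 df); the four-per-arm column uses m = 40.

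| ICC | Z power, two per arm | t power, two per arm (2 df) | t power, four per arm (6 df) |
|---|---|---|---|
| 0.001 (stated) | 83.5% | 38% | 70% |
| 0.01 (assumed) | 62% | 26% | 58% |
| 0.05 (assumed) | 28% | 13% | 32% |

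At ICC 0 the 2 df power is still only 40%, so the shortfall at the stated ICC comes almost entirely from the degrees of freedom. With two clusters per arm and ICC exactly 0.001, about 760 per arm would be needed for 80%. At ICC 0.01, power levels off near 46% however many women are enrolled.

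**3. The breakdown.** 2 × 168 = 336 women, and 336/4 = 84 per cluster, not 42. 4 × 42 = 168, which the text calls one arm. The pilot figures have the same pattern: 2 × 140 = 280, and 280/4 = 70 per area, not 35. In Recruitment and follow up, 35 is the target for each worker (8 × 35 = 280), so the word cluster may not denote the randomised area here.

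**The case against.** The best defence is that the figure is reproducible and is not a claim about the pilot. Both parts stand. A reader might infer that 160 does not follow from 20% and 15%; it does, under a standard variant, and the fault is that wording and calculation point in different directions.

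A reader might also go further and conclude that the right comparison is 80% vs 95% and that n should fall to 78–92. The documents do not establish this. The sentence joins antenatal visits with skilled delivery, the difference has no direction, and more than one clinical outcome is said to have been used. As an illustration only, the Background puts unattended births at about 40%; 60% vs 75% without continuity correction gives 151.9 × 1.039 = 158 to 151.9 × 1.079 = 164, again about 160. And 78–92 per arm for 80% vs 95% would have only 36–40% power on 2 df.

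Three other strong readings fail:
- That four clusters can never reach significance. This is true of a permutation test (smallest two-sided p = 2/6 = 0.33, or 2/4 = 0.50 if paired by district), but the article names no such test.
- That the pilot's size is derived from the faulty figure. The section does cite a rule setting a pilot at half the main trial, but 140 per arm is neither 160 or 168 nor half of either, and it is attributed to pilot rules.
- That the larger trial will have four clusters. The article says only that pilot results will inform it.

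The section does not say whether four clusters is a total or per arm, and 168/42 = 4 and 140/35 = 4 fit four per arm. That reading conflicts with the four areas described and still leaves about 70%. Finally, mean (SD) is a legitimate summary of a visit count, and visit attendance is recorded, so the proportion could still be derived.

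**Conclusion.** The concern holds for the power statement and for the wording of the inputs. With the four health areas described, the stated 80% is about 38% on the inputs that reproduce 160 per arm, and lower at any larger ICC; if four clusters per arm is meant, it is about 70%. These figures assume a cluster-level t comparison, equal cluster sizes, 160 women per arm analysed and an absolute 15-point difference. The base rate and direction as worded do not match the calculation that gives 160, and the 84 and 42 breakdown does not fit four clusters for 336 women. Which outcome and control rate were intended cannot be settled from the article. The consequence is confined to planning the larger trial: the pilot states no efficacy power, and its feasibility thresholds do not depend on this calculation. The Table 1 point is minor, and clearest for skilled delivery, a yes/no event for each woman.

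**What to change.** - Delete the 80% power statement, or restate it with the cluster-level degrees of freedom.
- State which outcome was used, its control rate on that outcome's own scale, the direction of the 15% difference, whether a continuity correction was applied, and whether four clusters is a total or per arm. Recompute n from those answers; do not assume 80% vs 95%.
- Correct the per-group and per-cluster breakdown so that it adds up over the randomised areas.
- Say that the larger trial will be sized by number of clusters over a range of ICCs.
- In Table 1, report skilled delivery and the proportion with more than two ANC visits as n (%) by health area and arm. The mean number of visits can stay alongside.

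The cost is one rewritten paragraph, small edits to Table 1 and a less favourable stated power. No extra participants are needed.
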